### Endpoints

The endpoints of the different research components will be quantitative (box 1), qualitative or mixed.

Box 1Trial interdisciplinary quantitative endpoints.Effectiveness endpointsPrimary endpoint: proportion of children started on treatment for tuberculosis (TB) among sick children attending care at participant health facilities for any health complaints.Proportion of children treated for TB among those with presumptive TB, including children with microbiologically confirmed TB.Proportion of children from high-risk groups treated for TB (age <2 years, children living with HIV, children with severe acute malnutrition) among all children from high-risk group attending care and among children from high-risk groups with presumptive TB.Proportion of children with TB who are microbiologically confirmed (ie, smear or Xpert or lipoarabinomannan positive), ratio of <5 years to 5–14 years among children with TB and ratio of pulmonary TB to extrapulmonary TB.Time from presumptive TB identification to final TB treatment decision and access to TB diagnostic assessment defined as the proportion of children with presumptive TB having completed assessment with the treatment decision algorithms (TDAs) and clinical decision support systemClinical Decision Support Systems, including in high-risk groups.Concordance of the TDA result and the final TB treatment decision using the proportion of children wrongly initiated or not initiated on TB treatment defined as: (1) children not started on TB treatment despite positive score; (2) children initiated on TB treatment despite negative score.Proportion of missed TB cases and over-diagnosed TB cases (unlikely TB with a positive score) compared to a reference standard diagnosis. This will be assessed in a subset of children with full diagnostic assessment (≥1 respiratory or stool sample tested with Xpert MTB/RIF Ultra, chest X-ray (CXR) availability, clinical evaluation and follow up) at district hospital or with access to CXR.Concordance of the severity evaluation and decision for short TB treatment regimen using the proportion of (1) children with 4-month TB treatment regimen used despite severe disease as assessed by the clinical/CXR evaluation; (2) children with 6-month TB treatment regimen despite non-severe disease as assessed by the clinical/CXR evaluation.Proportion of missed severe TB cases and cases over-diagnosed as severe, compared to reference standard severity assessment by expert at low level of health care: (1) children with non-severe disease according to clinical criteria despite severe disease as evaluated by expert CXR read; (2) children with clinically assessed severe disease despite non-severe disease as evaluated by expert CXR read.Proportion of children with presumptive TB and with non-severe TB disease initiated on shorter TB treatment.TB treatment outcomes as defined per WHO (treatment success, cured, treatment completion, loss to follow-up, death, treatment failure) overall and stratified by severity and regimen duration.Deaths averted assessed through modelling.Number of adults with TB, including microbiologically confirmed TB, and proportion of all TB diagnosed that is child TB.Acceptability endpointsCo-primary endpoints: clinicians stating that in their facility they are confident in their ability to decide to initiate TB treatment in a child <5 years/in a child 5–14 years.Secondary endpoint: clinicians stating that in their facility they are confident in their ability to decide to initiate TB treatment in a child.Secondary endpoints: clinicians stating that in their facility they are not over-diagnosing children <5 years/5–14 years/all children, that is, initiating children on TB treatment when they actually do not have TB.Secondary endpoints: clinicians stating that in their facility they are supporting children <5 years/5–14 years/all children with TB to access care/medication as swiftly as they should.Feasibility and implementation endpointsCo-primary endpoint: healthcare workers (HCWs) stating that in their facility they have the adequate tools to diagnose children <5 years for TB/5–14 years for TB*.Secondary endpoint: HCWs stating that in their facility they have the adequate tools to diagnose any children (<15 years) for TB*.Secondary endpoint: clinicians stating that in the last 3 months they started a child on TB treatment.Health economics endpointsa. Cost analyses of the standard of care (SOC) and of the comprehensive TDA-based approachTotal TB care costs from the health system perspective.Unit cost per TB care activity (eg, clinical assessment, CXR).Total TB care costs of overdiagnosis (false positive)—intervention only.Total costs incurred by parents/caregivers for receiving child TB care.b. Cost-effectiveness of the comprehensive TDA-based approach compared to the SOC:Modelled health impact measure:Number of children treated for TB.Number of adults treated for TB.Number of deaths.Disability-adjusted life years (DALYs): measure of healthy life lost, either through premature death or living with disability due to illness.Cost-effectiveness measure, that is, incremental cost per:Incremental number of children treated for TB.Death averted.DALY averted.c. Budget impact of the comprehensive TDA-based approach scale-up compared to the SOC over 5 years:Cost of scaling up the comprehensive TDA-based approach nationally.Cumulative number of children and adults treated for TB, lives saved and DALYs averted during a 5-year scale-up.

The primary effectiveness endpoint will be the proportion of children started on TB treatment among sick children attending care at selected facilities for any health complaint, calculated during the SOC and intervention periods. Secondary effectiveness endpoints include the calculation of other proportions (eg, proportion of children treated for TB—including with TB confirmed or at high risk for TB—among all children with presumptive TB, among all children from high-risk groups attending care, etc), disaggregated by age and TB status. Time between presumptive TB identification and treatment decision and initiation will be measured. Concordance between TDA results and TB treatment decision and between severity evaluation and short treatment regimen decision will be calculated. Diagnostic accuracy (sensitivity, specificity, negative and positive predictive values) of the TDAs and severity assessment accuracy will be assessed based on a reference standard determined by an endpoint review committee taking into consideration diagnostic and follow-up data.

The acceptability of the intervention will be reported as the preferences of HCWs in delivering childhood TB diagnosis and care (comparing the intervention vs SOC), the perceived social value of the intervention for HCWs and beneficiaries and the associated health systems and socioeconomic and contextual factors influencing overall acceptability.

The feasibility/implementation endpoints will be the feasibility of delivering and implementing childhood TB diagnosis and care and specifically the intervention; the fidelity to intervention delivery plan and adherence to implementation guidelines; the adaptations in implementation over time; the contextual factors influencing implementation and the sustained delivery of the intervention 6 months post implementation.

Health economics endpoints will include total TB care costs from both health system and patient perspectives and estimated unit costs per care activity. The cost-effectiveness of the TDA-based approach will be evaluated through incremental cost per children with TB diagnosed and treated, alongside incremental costs per death and disability-adjusted life years (DALYs) averted. Additionally, a 5-year budget impact analysis will estimate national implementation costs and endpoints such as cumulative cases treated, lives saved and DALYs averted.

Finally, health policy endpoints will be the roles and practices among implementers and decision-makers at the district level regarding the intervention, their perceived usefulness of the intervention, their option of the intervention and the mechanisms for translating research findings into public policies and practices.

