**Trial registration number:**

NCT06593080; PACTR202407866544155.

STRENGTHS AND LIMITATIONS OF THIS STUDYDecide TB will evaluate a comprehensive approach for screening, diagnosis and management of childhood tuberculosis (TB) using several treatment decision algorithms (TDAs) adapted to different paediatric population groups, including high-risk children. TDAs will be implemented at primary and secondary levels of healthcare, with the support of digital tools.Decide TB is a stepped wedge cluster-randomised trial embedded in a national TB programme-led programmatic pilot, with a hybrid effectiveness-implementation design in order to maximise transfer of research into policy and practice.Interdisciplinary mixed methods research will be used to assess effectiveness of TDAs, including TB detection, diagnosis accuracy of TDAs and key implementation research endpoints such as feasibility, acceptability, values and preferences, adoption, costs, cost-effectiveness and budget impact.The stepped-wedge design provides an opportunity to improve intervention implementation from one district to the next but at the same time limits the scope of continuous improvement of TDA implementation within each district.The quality of clinical data collected among children in routine conditions may be limited by the suboptimal use of digital tools due to functional and structural barriers within health facilities.

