## Methods and analysis

### Study type/study design

Decide TB is a pragmatic cluster-randomised trial (2024–2026) with a stepped wedge and hybrid effectiveness-implementation trial type 2 design. It will evaluate a comprehensive TDA-based approach (intervention) versus the SOC (control) for screening, diagnosis and treatment decision for childhood TB (see figure 1).^23^ Districts in each country will be randomly selected to successively initiate the intervention every quarter. Prior to the trial, a site selection survey will systematically identify districts and facilities that have the capacity to deploy TDAs and present a diversity of health systems and geographical characteristics.^24^ Formative research will describe the local facilities and community dynamics to highlight potential implementation barriers and facilitators and inform on intervention implementation strategies. The intervention will be implemented by the NTPs of Mozambique and Zambia. The effectiveness of the intervention in terms of TB case detection (children started on TB treatment) among children attending care will be assessed by comparing it to the SOC using both aggregated and register-based individual routine health data from the Ministry of Health (MoH). Additionally, aggregated and register-based individual data will be collected retrospectively for 12 months for secondary effectiveness endpoints (table 1). We will develop an electronic medical record (EMR) to collect individual health data among all children with presumptive TB. The EMR will be developed in Demographic Health Information System 2 (DHIS2) using the same variables for both countries. The diagnostic accuracy of the SOC and of the intervention will be assessed in an additional district in each country not participating in the stepped wedge design. The acceptability, feasibility, health economics and health policy evaluations of the intervention and of its implementation will be nested within the trial and use repeated mixed method surveys (in a convergent design). The study will start with formative research in February 2024. The stepped wedge trial will start mid-2024 and end mid-2026. The last children enrolled during the trial will be followed up until the end of 2026. A post-intervention sustainability survey will take place early 2027. Both countries will be autonomous in terms of trial start date and analysis.

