**Figure 1 F1:**
[figure not shown]
Overall study design at the country level. SOC, standard of care; TDA, treatment decision algorithm.

**Table 1 T1:** Data collection and tools

	Site selection and formative research	Effectiveness	Acceptability	Implementation	Health economics	Health policy	Timing of data collection *Target population*	Data collected *Data collection method*
Aggregated data	X	X					Retrospective, SOC, intervention and follow-up *Children attending care, children with TB*	Aggregated health data routinely reported to the MoH in the national DHIS2 database including OPD attendance, number of children in high-risk groups, number of TB notifications in children, among others.
Individual data-based registers		X					Retrospective, SOC, intervention and follow-up *Children with presumptive TB and TB*	Data from presumptive TB registers and from TB treatment registers *Reported in created modules in DHIS2*
EMR		X					SOC in additional district only and intervention *Children with presumptive TB*	Demographics, clinical and anthropometric data, HIV status, radiological data and abdominal ultrasound examination, laboratory data, TDA used and score, TB severity assessment, TB treatment if initiated and duration, TB treatment outcomes, comorbidity management including antiretroviral treatment, nutrition therapy and status at follow-up visit *EMR data entry on tablet in DHIS2*
Child TB questionnaire	X		X	X			Formative phase and before end of trial *HCWs*	Knowledge, attitudes and practices of HCWs, their readiness to and their perceived feasibility of TDAs for childhood TB. *Self-administered REDCap questionnaire on tablet, with support from social sciences research assistants (SSRAs*).
TB diagnosis questionnaire			X	X			Quarterly (implementation and intervention) 6 monthly (acceptability) *HCWs*	Structured in three modules: (1) implementation module, to assess the scope of childhood TB diagnosis activity, barriers and facilitators and context; (2) acceptability module, to document perceptions of appropriateness of, utility of and self-confidence towards the diagnostic approach used in the facility; (3) intervention module (intervention arm only), to document the experience of the comprehensive TDA-based approach. *Self-administered REDCap questionnaire on tablet, with support from SSRAs*

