### Implementation strategies

Implementation strategies supporting intervention deployment will be aligned with the routine NTP implementation plans of both countries. District-level training for HCWs on TDA use, digital tool use and interpretation of imaging results will include initial face-to-face training, cascade training to other facility staff members and continuous training supported by digitalised training and support material. Monthly (first 3 months), then quarterly support supervision visits and clinical mentoring visits will be organised both on-site and online; these visits will address implementation bottlenecks and reinforce clinical skills. NTPs will lead the procurement of equipment and supplies to ensure clinicians have access to adequate sampling and testing materials and supplies for the optimal use of TDAs in the field. Continuous coordination meetings will be organised. Community mobilisation activities within facility catchment areas and districts overall will include community meetings and radio shows.

National data collection systems for childhood TB/integrated management of childhood illness will be strengthened for routine programme monitoring and for trial data collection, through the use of the DHIS2 platform on tablets. At the facility level, the EMR will be completed on tablets to report individual data for each child with presumptive TB: demographic, clinical and other data needed to calculate TDA scores and to assess disease severity. The CDSS, interconnected with the EMR module, will extract the children’s characteristics and facility profile data to orient on the choice of the TDA data and to calculate the TDA scores.

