### Data collection and tools

For the effectiveness component, aggregated data originally obtained from facility registers and entered in the national DHIS2 database will be extracted; individual data from registers (TB treatment and TB presumptive registers) will also be entered on specific DHIS2 modules, in addition to the EMR. For the analysis of endpoints collected at the intervention phase and the diagnostic accuracy assessment, we will use the individual patient data collected in the EMR. For the acceptability, feasibility/implementation and policy components, we will use both quantitative data (child TB questionnaire, TB diagnosis questionnaire) and qualitative data (interviews, supervision and clinical mentoring reports, field notes). The health economics component will use questionnaires. Quantitative data from the acceptability, feasibility/implementation, health economics and policy components will be entered on the electronic data capture application Research Electronic Data Capture (REDCap; https://www.project-redcap.org/). Interviews will be captured on audio-recording devices (with respondent consent) and electronically typed/transcribed. Table 1 details the data collected, tools and methods contributing to the research components and endpoints.

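### The EMR is the named source for intervention-phase endpoints, so the secondary TDA-access endpoint would be overstated wherever EMR entry is incomplete; its denominator should come from the presumptive TB register

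*Protocol article*

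**What the plan says.** Box 1 (section Endpoints) lists, among the effectiveness endpoints after the primary one, "access to TB diagnostic assessment defined as the proportion of children with presumptive TB having completed assessment with the treatment decision algorithms" and the CDSS, overall and in high-risk groups. The definition does not name a data source.

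The source is given in Data collection and tools: for endpoints that arise in the intervention phase, and for diagnostic accuracy, the article says "we will use the individual patient data collected in the EMR". The preceding sentence of that section adds that "individual data from registers (TB treatment and TB presumptive registers) will also be entered on specific DHIS2 modules, in addition to the EMR". Table 1 describes the register source as "Data from presumptive TB registers and from TB treatment registers" and gives its timing as retrospective, standard of care, intervention and follow-up.

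The EMR is meant to be complete. Study type/study design says "We will develop an electronic medical record (EMR) to collect individual health data among all children with presumptive TB", and Implementation strategies says "the EMR will be completed on tablets to report individual data for each child with presumptive TB". Implementation strategies also describes the CDSS as connected to the EMR module and drawing the child's characteristics from it. The strengths and limitations list warns that the quality of routine clinical data may suffer from "suboptimal use of digital tools due to functional and structural barriers within health facilities".

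**The concern.** An uptake measure needs a denominator that does not depend on the thing being taken up. Here the CDSS runs on EMR data, and the EMR is the named source for intervention-phase endpoints. If the same EMR supplies the list of presumptive-TB children, a child whom staff identified and wrote in the register but never entered on the tablet is lost from both numerator and denominator. Under the Box 1 definition that child did not complete the assessment and should count as a failure.

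The error has one direction. Omitting certain non-completers can only raise the proportion. The effect is largest where the tablet is used least, and those facilities also contribute the fewest children to a pooled EMR figure.

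What is at stake is a patient-level proportion in a hybrid effectiveness-implementation trial. The quantitative feasibility endpoints in Box 1 are statements by healthcare workers, and concordance between score and decision can be assessed only in children who have a score. An inflated access figure would make a weak effectiveness result harder to interpret.

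**Working it through.** The article gives no target, expected value or sample size for this endpoint, so there is no figure of the plan to reproduce. The check has two parts: which source applies, and what follows if it is incomplete.

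**Which source applies**

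1. Completion of the TDA and CDSS assessment can be observed only once the intervention has started in a stepped-wedge district. It is therefore an intervention-phase endpoint.
2. Data collection and tools assigns such endpoints to the EMR.
3. Effectiveness endpoints, under Data analysis, assigns aggregated or register data to endpoints compared between standard of care and intervention. This endpoint has no such comparison, so that rule does not clearly cover it.
4. Nothing in the article takes the denominator of this endpoint from the register or compares EMR entries with register entries. Nothing excludes the register either.

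**What follows**

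Let N be the children with presumptive TB in a facility and period, c the share of them entered in the EMR, and u the share of EMR children who complete the assessment. Neither c nor u is given; both are assumptions. Children outside the EMR count as non-completers, because the CDSS needs EMR data.

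- EMR denominator: (N × c × u) / (N × c) = u
- All presumptive children as denominator: (N × c × u) / N = c × u
- Overstatement: u − c × u = u × (1 − c); as a ratio, 1/c

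With u = 0.90 assumed:

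| Assumed coverage c | EMR-only figure | True access c × u | Overstatement (points) | Ratio 1/c |
|---|---|---|---|---|
| 1.00 | 90% | 90% | 0 | 1.00 |
| 0.95 | 90% | 85.5% | 4.5 | 1.05 |
| 0.90 | 90% | 81% | 9 | 1.11 |
| 0.80 | 90% | 72% | 18 | 1.25 |
| 0.70 | 90% | 63% | 27 | 1.43 |
| 0.50 | 90% | 45% | 45 | 2.00 |

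Over the assumed ranges c = 0.50 to 0.95 and u = 0.60 to 0.95, the overstatement runs from 0.60 × 0.05 = 3 points to 0.95 × 0.50 = 47.5 points. At c = 1 it is zero.

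The same table shows the loss of contrast between facilities. Two facilities with coverage of 90% and 50%, and the same u, would both show 90%, although their true access is 81% and 45%.

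**The case against.** The strongest reply is that the article never restricts the denominator to EMR records. Box 1 says children with presumptive TB, the EMR is designed to include every one of them, and register data are collected in parallel under the effectiveness component. A reader might infer that the plan has decided to compute access only among EMR children and that the result is therefore overstated. The documents do not support that as a fact. The restriction is an inference from one general sentence about sources, and overstatement requires incomplete entry, which is not quantified. The warning about digital tools is about data quality; missing entries are one possible form of suboptimal use, not a stated expectation. All of this stands, and the point is conditional for that reason.

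A second reply is that denominators of secondary endpoints belong in the statistical analysis plan, which is not shown. Silence would indeed be no finding. Here, however, the article names a source, and for an uptake measure that source is circular.

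A third reply is that delivery is also followed through fidelity and adherence assessment, supervision and mentoring reports, facility observations, and the intervention module of the TB diagnosis questionnaire. That stands too. A reader might infer that the trial could not tell an ineffective approach from one that was not delivered, or that this is its main measure of delivery. Neither follows: Box 1 gives the endpoint no such rank, and the other sources carry information, although the article does not show them yielding this proportion.

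Finally, registers can under-record, and the article does not show that they record HIV or nutritional status. This limits the remedy and is taken into account there.

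**Conclusion.** The point holds in conditional form. On the plain reading of Data collection and tools, the access endpoint would take both numerator and denominator from the EMR. Children never entered would then disappear instead of counting as failures, and access would be overstated by a factor of 1/(EMR coverage) whenever coverage is below 100%. The direction is certain under that reading. The size is unknown, because the article gives neither coverage nor completion; the figures of 81%, 63% and 45% against 90% are illustrations that rest on assumed values of both. If every presumptive child is entered there is no bias, but the article describes no check that would show this.

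It would be wrong to extend the point to the main result. The primary endpoint is the proportion started on treatment among children attending care, based on routine aggregated or register data, and neither it nor its power statement depends on EMR coverage. This is one secondary endpoint that needs a better-specified denominator.

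**What to change.** In Box 1 or Data collection and tools, and in the statistical analysis plan, specify for this endpoint:

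- **Denominator:** children in the presumptive TB register of the same facility and period.
- **Numerator:** EMR records with a completed TDA and CDSS assessment.
- **Coverage:** EMR presumptive-TB count divided by register count, reported by facility and quarter. Facilities where the EMR count exceeds the register count should be flagged as register under-recording.
- **High-risk groups:** use the register denominator only where the register records the risk factor. Otherwise label the estimate as EMR-only and show it beside coverage.

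Facility-quarter counts are enough for this; individual linkage is not needed. Both sources are already collected during the intervention phase, so the cost is wording and one coverage table. The downside is that reported access will be lower where coverage is incomplete, and that the estimate then depends on how completely the registers are kept.
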